## Abstract

**Background:**

Cognitive impairment is common in haemodialysis (HD) patients and is associated independently with depression and mortality. This association is poorly understood, and no intervention is proven to slow cognitive decline. There is evidence that cooler dialysis fluid (dialysate) may slow white matter changes in the brain, but no study has investigated the effect of cooler dialysate on cognition. This study addresses whether cooler dialysate can prevent the decline in cognition and improve quality of life (QOL) in HD patients.

**Methods:**

This is a multi-site prospective randomised, double-blinded feasibility trial. Setting: Four HD units in the UK. Participants and interventions: Ninety HD patients randomised (1:1) to standard care (dialysate temperature 36.5 °C) or intervention (dialysate temperature 35 °C) for 12 months. Primary outcome measure: Change in cognition using the Montreal Cognitive Assessment (MoCA). Secondary outcome measures: Recruitment and attrition rates, reasons for non-recruitment, frequency of intradialytic hypotension, depressive symptom scores, patient and carers burden, a detailed computerised cognitive test and QOL assessments. Analysis: mixed method approach, utilising measurement of cognition, questionnaires, physiological measurements and semi-structured interviews.

**Discussion:**

The results of this feasibility trial will inform the design of a future adequately powered substantive trial investigating the effect of dialysate cooling on prevention and/or slowing in cognitive decline in patients undergoing haemodialysis using a computerised battery of neuro-cognitive tests. The main hypothesis that would be tested in this future trial is that patients treated with regular conventional haemodialysis will have a lesser decline in cognitive function and a better quality of life over 1 year by using cooler dialysis fluid at 35 °C, versus a standard dialysis fluid temperature of 36.5 °C. This also should reflect in improvements in their abilities for activities of daily living and therefore reduce carers’ burden. If successful, the treatment could be universally applied at no extra cost.

**Trial registration:**

ClinicalTrials.gov NCT03645733. Registered retrospectively on 24 August 2018.

## Background

Increasing severity of chronic kidney disease (CKD) is associated with a gradual increase in prevalence of cognitive impairment [1, 2] independent of vascular risk factors [3]. Different diagnostic methods influence the definition and incidence of cognitive impairment, but recent reviews suggest the presence of at least moderate cognitive impairment in 30–70% of haemodialysis (HD) patients [4–6]. Cognitive impairment in HD patients is associated independently with higher rates of depression and mortality [4, 7], although this association is likely complex and poorly understood. Severe depression can even mimic cognitive impairment making it important to measure depression rates in studies of cognitive impairment to understand the interaction. Traditional atherosclerotic risk factors [7] cannot entirely account for the excess risk of cognitive impairment [8]. Multiple HD specific factors including oxidative stress, malnutrition and inflammation are implicated [9]. The process of HD does not remove toxins as efficiently as the native kidney and accumulation of several neurotoxins [10] may also act to reduce brain perfusion and compromise blood-brain barrier integrity [11]. The process of HD involves cycles of removing varying volumes of fluid, electrolytes and toxins that accumulate between treatments. Intradialytic hypotension is common affecting 30–40% of treatments and is associated with at least a 30% increase in mortality and reduced quality-of-life (QOL) [12]. Left ventricular hypertrophy and aortic stiffness are seen in most HD patients and further lower diastolic coronary perfusion. The result is that HD might be seen as a process that frequently involves repeated ischemic insults to the brain and other organs [13–15]. These dynamic changes in blood pressure (BP) and perfusion might be associated with altered cognition, but supporting data are sparse and conflicting, possibly reflecting differences in study design such as different methods and timings of cognitive assessment. Several small studies show cognition is best immediately before HD, becomes worse during HD and then improves the day after with a possible link to acute fluid removal [16, 17]. Absence of intradialytic hypotension is emerging as a novel treatment goal and it is plausible that preventing intradialytic hypotension might prevent intradialytic brain ischemia and slow the development of cognitive impairment in HD patients [18]. One method that may prevent intradialytic hypotension is to increase treatment time or frequency to allow a slower rate of fluid removal [19]. A preliminary repeated measures study of 12 patients showed extended overnight HD was associated with improved cognition measured by a battery of neuropsychological tests [20]. These data are encouraging but come at the expense of increased treatment complications, cost and are currently not feasible in most centres in the UK and worldwide. The use of cooler dialysate (34–35 °C) to prevent intradialytic hypotension was first described in 1981 [21], but remains underused because of perceptions about thermal symptoms [22–24]. Cooler dialysate is thought to prevent intradialytic hypotension by preventing a rise in core temperature and subsequent systemic vasodilation [25]. A recent systematic review showed that compared with standard temperature dialysis, cooler dialysis reduced the event rate of intradialytic hypotension by 70% (95% CI, 49–89%) [24]. A recent pilot clinical trial in 38 patients showed lower temperature of dialysis fluid applied for one year prevented worsening of baseline ischaemic brain white matter change through ameliorating haemodynamic instability [26, 27]. A trial also reported cooler dialysis fluid improved cardiac structure and function [28]. While these results show the potential for dialysate cooling as a cardioprotective and neuroprotective treatment, the effects of cooler dialysate on cognition, QOL and illness burden remain unknown. There is also little information about how cooler dialysis fluid is tolerated. The current low usage of cooler dialysate in the UK affords an opportunity to definitively test this simple modification to HD as a potential intervention to prevent cognitive impairment and increase QOL. There remain several uncertainties around study design of a definitive trial of cooler dialysate and cognitive impairment; hence, there is a need to assess this formally in a feasibility study.

## Methods

We aim to perform a feasibility trial that will inform the development of a definitive, fully powered, randomised, controlled clinical trial that would examine the efficacy of cooler dialysis fluid in reducing cognitive decline in patients receiving HD for End-Stage Kidney Disease (ESKD). The main hypothesis that would be tested in this future trial is that patients treated with regular conventional HD will have a reduced decline in cognition and a better QOL over 1 year by using cooler dialysis fluid at 35 °C, versus patients treated using a standard dialysis fluid temperature of 36.5 °C.

### Primary objective

The primary objective is to test the feasibility of the investigation of lower temperatures of dialysis fluid in preventing the decline in cognitive function and improve the quality of life in HD patients.

### Secondary objectives

To provide an estimate of the variability in the outcome measures for the cooled dialysis and standard treatment arms, to inform a future, adequately powered, definitive trial.To measure the frequency of intradialytic hypotension as an explanatory outcome.To measure recruitment and attrition rates to inform the design of a larger clinical trial.To record reasons for non-recruitment and study attrition to inform the design of a larger clinical trial.To measure baseline levels of depression in the targeted population to inform estimates of exclusion rates for participants with depressive pseudo cognitive impairment from the future trial.To assess the burden of study-related interventions and assessments on patients and carers.To assess the administration, suitability and adherence of the chosen method for assessment of cognition in patients, especially in those from ethnic minorities.To assess the administration and suitability of the chosen QOL scales and activities of daily living in HD participants.To assess the administration and suitability of the chosen method for measuring carers’ burden in this group.

The protocol will be considered viable for a definitive RCT without modification if the following outcomes are met:
Recruitment rates of at least 50% of eligible patients;Attrition rate of < 20% by 6 months;Compliance rate of 60% to trial.

If these outcomes are not met, the protocol will be modified in light of the study’s findings.

We used the Standard Protocol Items: Recommendations for Interventional Trials (SPIRIT) checklist when writing our report [29].

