### Outcome measures

#### Primary outcome measure

The primary outcome measure is change in cognition from baseline to 12 months, assessed by Montreal Cognitive Assessment (MoCA, v7.2) [31], in the standard and low temperature dialysis groups.

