### Data analysis

Data analysis will be performed by statisticians who are blinded to participant treatment allocation. A mixed method approach will be used, utilising semi-structured interviews, questionnaires and measurement of cognitive function. The 12 month follow-up period will be the key assessment time for all outcomes. Normally distributed data will be presented as mean (SD), skewed data as median (IQR) and categorical data as number (percent). The main aim of the qualitative component is to assess issues related to patient recruitment. This will include practicalities of implementing cooler dialysate, adherence to treatment, effectiveness of blindness process and identification of factors that may affect routine practice of treatment in various centres. We will apply thematic analysis to qualitative data collected from semi-structured interviews. Interviews will be on a 1:1 basis and will be audio-recorded. They will be transcribed by the research assistant and will be anonymised and securely stored, accessible only by the research team. The purpose of the quantitative analysis is to estimate the mean and standard deviation for MoCA at baseline and follow-up in both trial arms and obtain an estimate of the attrition. For all analysis, the level of significance will be set at 5%, so that 95% confidence intervals will be presented. This is a feasibility study and statistically or clinically significant changes in outcomes between groups are unlikely; hence, no between-group inferential comparisons will be made. However, a preliminary estimate of a treatment effect is relevant to sample size estimation of future definitive trials. As an exploratory analysis, we will conduct a complete case analysis of the primary and secondary outcomes. A linear regression model will be used for continuous outcomes (e.g. MoCA) and a logistic regression model will be used for binary outcomes. Each model will include the baseline measurement and treatment arm as independent variables. All patients randomised to their respective study arms will be included in the intention to treat analysis. Missing data, if any, will be managed using the last-observation carried forward approach. There will be no interim analysis of the data, though the safety data resulting from any SAE will be collated and made available to the Trial Steering Committee. All analysis will be conducted in Stata 15.

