### Sample size

The outcome data from this feasibility study will be used to inform the sample size calculation for the definitive trial, by providing estimates of the primary outcome and its variability and the expected attrition. The study aims to recruit a total of 90 patients from four sites. Lancaster and co-workers outlined the key aspects of feasibility studies and indicated at least 30 patients per each arm are required to identify the sample variability (standard deviation) in key variables to enable the calculation of power for testing hypotheses in subsequent definitive studies [46]. The primary outcome in the definitive study is likely to be a value from the MoCA. With 45 patients in each arm, and if the mean (SD) value of the MoCA is 27 (2) in the control and intervention arms at the study start, we could expect a 95% confidence interval to range from 26.4 to 27.6 in each arm. This will give adequate precision for the estimate required in the study. With 45 patients in the control arm, and assuming a mean (SD) value of MoCA of 22 (3) after 12 months, we could expect a 95% confidence interval to range from 21.1 to 22.9. In the intervention arm, assuming a mean (SD) MoCA value of 25 (3) after 12 months, we could expect a 95% confidence interval to range from 24.1 to 25.9. Furthermore, with a total sample size of 90 patients, with an expected loss of 20% of the patients, a 95% confidence interval could be produced, ranging from 70.2 to 87.7%.

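### The only attrition condition in the viability rule is read at 6 months, so the protocol can be declared viable unmodified whatever the loss between 6 and 12 months

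*Protocol article*

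**What the plan says.** Secondary objectives in the protocol article gives the decision rule: "The protocol will be considered viable for a definitive RCT without modification if the following outcomes are met". Three conditions follow, on recruitment, attrition and compliance. The attrition condition is "Attrition rate of < 20% by 6 months". The compliance condition is "Compliance rate of 60% to trial", with no definition and no time point. If the conditions are not met, the protocol is to be modified.

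The other time anchors are at 12 months:
- Primary outcome measure: "The primary outcome measure is change in cognition from baseline to 12 months".
- Data analysis: "The 12 month follow-up period will be the key assessment time for all outcomes".
- Methods, on the hypothesis of the definitive trial: "a reduced decline in cognition and a better QOL over 1 year by using cooler dialysis fluid at 35 °C".
- Randomisation and concurrent treatments: both dialysate temperatures are allocated for 12 months.

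Sample size gives a precision statement for 90 patients "with an expected loss of 20% of the patients" and does not say by when that loss is expected.

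**The concern.** A progression criterion on attrition should show whether enough patients reach the endpoint of the trial being planned. Here that endpoint is the 12-month MoCA, but the criterion stops at the halfway visit. A feasibility trial that keeps its patients to month 6 and loses many afterwards meets the attrition condition exactly as well as one that loses nobody afterwards.

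Nothing else in the rule fills the gap. The compliance condition is undefined, and even if read as retention it would accept 40% loss. At stake is the decision to run the definitive trial without changing its follow-up or retention arrangements. No estimate or interval in the feasibility trial itself is affected.

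**Working it through.** **Inputs.** 90 patients, 45 per arm (Study setting and population). Attrition limit below 20% at 6 months (Secondary objectives). Expected loss 20%, time point not stated (Sample size). The pattern of loss between 6 and 12 months is not given, so it is an assumption and is varied below.

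**The plan's own figure.** With 20% lost, 72 of 90 remain. The exact (Clopper–Pearson) 95% interval for 72/90 is 70.25% to 87.69%, which agrees with the 70.2 to 87.7% in Sample size. That figure is not in dispute.

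**Largest passing count.** 18/90 = 20.0% is not below 20% and fails. 17/90 = 18.9% passes and leaves 73 patients at 6 months.

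**Loss at 12 months.** Let a be the loss by 6 months and h the proportion of those remaining who are lost in months 6 to 12. Then 12-month loss = 1 − (1 − a)(1 − h). With a = 17/90:

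| h (assumed) | Patients left, 73 × (1 − h) | Per arm | 12-month loss |
|---|---|---|---|
| 0% | 73.0 | 36.5 | 18.9% |
| 5% | 69.4 | 34.7 | 22.9% |
| 10% | 65.7 | 32.9 | 27.0% |
| 15% | 62.1 | 31.0 | 31.1% |
| 18.9% (same as first half) | 59.2 | 29.6 | 34.2% |

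From 17 lost at 6 months, one further loss gives 18/90, which would breach the 20% limit if it were read at 12 months.

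**How often the rule passes.** Assume a constant loss rate, so that 12-month loss is 1 − (1 − a)². The pass probability is the binomial P(X ≤ 17) with n = 90, taken at the 6-month loss for the present rule and at the 12-month loss if the same limit were moved to 12 months.

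| True 6-month loss | True 12-month loss | Present rule passes | Same limit read at 12 months |
|---|---|---|---|
| 15% | 1 − 0.85² = 27.75%, about 28% | 0.88 | about 0.03 |
| 18% | 1 − 0.82² = 32.76%, about 33% | 0.65 | about 0.002 |
| 20% | 1 − 0.80² = 36.0% | 0.46 | below 0.001 |

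The last column uses the rounded losses of 28%, 33% and 36%.

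**Equivalent early check.** Under the same assumption, 20% loss at 12 months corresponds to 1 − √0.80 = 10.6% at 6 months, or about 9 of 90.

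**Cost of moving the limit unchanged.** If true 12-month loss were exactly 20%, P(X ≤ 17 | n = 90, p = 0.20) = 0.46, so the criterion would be missed about 54% of the time.

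**The case against.** The best case for leaving the rule alone is that 12-month loss will not go unseen. Attrition and its reasons are secondary outcomes. Sample size says the study will supply the expected attrition for the definitive calculation. The Trial Steering Committee reviews data at least every 6 months and advises on the potential full study. Attrition is also only one of three joint conditions, so the pass probabilities above describe that condition and not the whole decision. All of this stands. It shows that the information will exist, but not that the written rule uses it: the rule is met or missed without reference to 12-month loss.

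Later loss may also be slower than early loss. The temperature is stepped down in the first weeks, so intolerance could cause early withdrawals. Patients expected to survive less than a year, or with a living-donor transplant date within the trial, are excluded. That is a fair reason not to rely on a constant rate alone, and it is why the range is shown.

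Three stronger readings are tempting, and the documents do not support them.
- **That the rule lets through a loss of over a third, with fewer than 30 per arm.** Projecting 20% at 6 months to 36% starts from a count that fails. Among passing counts only 17/90 projects above a third (34.2%, 29.6 per arm), and only at a constant rate. At 16/90 the figures are 32.4% and 30.4 per arm.
- **That the rule tolerates nearly twice the planned attrition.** This needs the 20% in Sample size to be a 12-month figure. Its position after the 12-month MoCA projections suggests so, but no time point is given. Read at 6 months, it agrees with the criterion.
- **That the rule breaches the plan's own minimum completion.** The statement that "at least 30 patients per each arm are required to identify the sample variability" concerns estimating a standard deviation in this feasibility study. It is not a retention standard for the definitive trial, and changing the viability rule would not change how many patients complete this one.

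**Conclusion.** The point holds in a limited form. The mismatch between a 6-month attrition condition and a 12-month endpoint is explicit in the text and needs no assumption. Its size does need one. At the largest passing count, 12-month loss runs from 18.9% with no later loss to 34.2% if the second half repeats the first. Under a constant loss rate, the present condition passes with probability about 0.88 and 0.65 at true 12-month losses of about 28% and 33%. The same limit at 12 months would almost never pass at those losses. The time point therefore largely decides the answer the criterion gives. The 20% level is the sponsor's choice and is not itself an error. The defect concerns the progression decision and leaves this trial's own estimates untouched.

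**What to change.** 1. State the attrition criterion at 12 months, with attrition defined as no 12-month MoCA, and report it with its 95% confidence interval.
2. Let the sponsor choose the limit consistently with the loss the definitive trial would be sized for. Carrying 20% over unchanged is one option, but its pass probability of about 0.46 at a true loss of 20% should be known when it is chosen.
3. If a 6-month reading is wanted, keep it only as an early check at a level consistent with the 12-month limit, and state the assumed pattern of loss that links the two.
4. Under Sample size, say by when the 20% loss is expected.

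The cost is a line or two of text and no new data collection, since the 12-month visit is already scheduled. The viability decision has to wait for 12-month data, and the criterion becomes harder to meet.

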### Study design

The schedule of events is summarised in Fig. 1 and Table 1. The study is a multi-site, prospective, randomised, double-blinded, controlled, feasibility trial [30].

**Fig. 1 Fig1:**
[figure not shown]
Study flow chart

**Table 1 Tab1:** Study schedule of data collection and assessments

	Baseline (O month)	6 months	12 months
Consent	X		
Randomisation	X		
Baseline data (defined)	X		
Cognitive function:			
Montreal Cognitive Assessment [31]	X	X	X
Cogstate [32]	X	X	X
Confusion Assessment Method [33]	X	X	X
Tolerability of Low Temperature Dialysis Questionnaire	Every 2 weeks for the first 6 weeks		
Activities of daily living:			
Assessment of QoL [34]	X	X	X
Bristol Activities of Daily Living Scale [35]	X	X	X
Carer burden assessment [36]	X	X	X
Hospital Anxiety and Depression Scale [37]	X	X	X
HD recovery time [38]	X	X	X
Qualitative interview			At completion or drop out
Dialysis temperature recording	During each HD session		
Physiological measurements*	During each HD session		
Laboratory measurements**	Measured monthly as part of routine care		
Adverse event reporting	X	X	X
Review Concomitant Medications	X	X	X

*MoCA* Montreal Cognitive Assessment tool, *CAM* Confusion Assessment Method, *QoL* quality of life, *ADL* activities of daily living, *HADS* Hospital Anxiety and Depression Scale

*Blood pressure (pre and post HD), intradialytic hypotension, nursing interventions for intradialytic hypotension, intradialytic weight gain over preceding 1 month

**KT/V as markers of adequate solute clearance, routine haematology and biochemistry

### Study setting and population

Patients will be recruited through the renal clinics at four HD units in the United Kingdom at Birmingham Heartlands Hospital, Runcorn Road Renal Unit, Solihull Hospital and Castle Vale Renal Unit. All these HD units are under the collective organisation of the University Hospitals Birmingham NHS Foundation Trust. The study aims to recruit 90 patients allocating 45 patients in the intervention and 45 patients in the control group. Suitable patients will be identified by the direct care team. The care team will speak with the suitable patients to see if they are happy to have their details passed on to the research team for further discussion. If the patient agrees, the research team will contact the patient and determine eligibility. Suitable patients will be identified through searching records in the four participating units. An information pack will be given to the patient (see Additional file 1), who will be given 24 h to read the information and ask any questions they may have. The research team will then contact the patient, in a pre-agreed manner (i.e. next clinic visit, via telephone) to see if they have any further questions or would like to participate in the study. If they would like to participate in the study they will arrange to meet and complete the consent form (see Additional file 2).

